### Statistical methods

#### Major statistical analysis

To examine the treatment effect parameters of all randomly assigned subjects in the primary analysis set, we will analyze the primary outcome according to the intention-to-treat principle. The significance level will be 5% and one-sided. The analysis was based on the analysis of a previous randomized, wait-listed, controlled trial of psychotherapy in cancer patients [48]. First, two-way repeated measures analysis of variance (ANOVA) will be conducted to examine the main effect of the intervention based on intervention status, with timing (pre-intervention, post-intervention, and 4 months post-intervention) and intervention status (intervention group and waiting group) as the independent variables and the primary endpoint, BDI-II score, as the dependent variable. Next, one-way repeated measures ANOVA will be conducted to integrate data from the intervention and waiting groups and to examine changes in BDI-II scores by time (pre-intervention, post-intervention, and 4 months after intervention) in both groups. When there is any missing data, we will employ multiple imputation.

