**Methods:**

A randomized controlled trial with a wait-list control group (waiting group) of 38 patients with advanced cancer and depression will be conducted at three sites in Japan. The BA program consists of seven sessions. Outcome measures will be evaluated at three times in the intervention group; at the entry, at the end of the intervention and 4 months after the end of the intervention and four times in the waiting group: at the entry, before the intervention, at the end of the intervention, and 4 months after the end of the intervention. Primary outcome is Beck Depression Inventory-II (BDI-II) score. To examine the main effect of the intervention, two-way repeated measures analysis of variance (ANOVA) will be conducted, with timing and intervention status as the independent variables and BDI-II score as the dependent variable. One-way repeated measures ANOVA will be conducted to combine data from the intervention and control groups and examine changes in BDI-II scores by timing in both groups. Secondary endpoints (anxiety, quality of life, spirituality, degree of behavioral activation, value, and pain) will be evaluated with rating scales. Two-way repeated measures ANOVA will be conducted to examine whether there are differences between the groups before and after the intervention, with timing and intervention status as the independent variables and scores on each rating scale as the dependent variables.

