The intervention and each assessment scale will be evaluated using the following process (Figs. 1 and 2). The University Hospital Medical Information Internet Data and Information System for Clinical and Epidemiological Research (UMIN INDICE) allocation software program will be used for case enrollment and randomization of intervention groups in this study. Randomization was stratified by study site with the minimization method to balance the gender (male, female) and the age of the participants at study entry (age 20 ≦ to < 40, age < 65, age 65 to < 100). For allocation concealment to research assistants who administer questionnaires, the allocation will be communicated to the person in charge at each site based on the allocation list prepared by the data center. In addition, the interval between T1 and T2, T2 and T3, T3 and T4 will be 4 months respectively, which is the same length of time it would take if the intervention group had implemented the program, so that research assistants will not be able to identify the allocation group based on the timing of evaluations. The allocation schedule will be kept at the data center until the end of the study. A psychiatrist or psychologist from each institution will be in charge of a total of seven intervention sessions. Outcome measures will be evaluated at three times (T1–T3) in the intervention group and four times (T1–T4) in the waiting group by research assistants who are not involved in the intervention program. Outcome measures will include the BDI-II score as the primary outcome measure and Generalized Anxiety Disorder-7 (GAD-7), Functional Assessment of Cancer Therapy-General (FACT-G), Functional Assessment of Chronic Illness Therapy - Spiritual Well-Being 12 Item Scale (FACIT-Sp-12), Behavioral Activation for Depression Scale-Short Form (BADS-SF), the Valuing Questionnaire (VQ), Numerical rating scale (NRS), and the Integrated Palliative care Outcome Scale (IPOS) scores as secondary outcome measures.

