### Power and sample calculation

Based on the results of a previous study [47], the minimal clinically important difference of the primary endpoint, BDI-II, is 3.5 points. In our pre-post study of patients with cancer and depression [26], the standard deviation was 7.84 points. Many studies have demonstrated the effectiveness of BA in depression with a high level of evidence [23–25]. We hypothesized an alternative hypothesis that intervention group would have lower mean post-intervention scores on the BDI-II than waiting group. The sample size was calculated using a one-tailed test with α = 0.05, power (1-β) = 0.80, and r = 0.50 for the mean value of the two groups. Since 3 (9.4%) out of 32 participants dropped out of the aforementioned pre-post study [26], we assumed that 10% would drop out in this study as well, defined as patients that did not meet the exclusion criteria and discontinued participation. Thus, the total planned enrollment was set to 38 patients.

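### The primary test, a main effect of randomised group over three times, does not estimate the hypothesised post-intervention difference, because the waiting group is treated after T2

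*Protocol article*

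**What the plan says.** All places are in the protocol article.

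- **Primary test** (Major statistical analysis): "two-way repeated measures analysis of variance (ANOVA) will be conducted to examine the main effect of the intervention based on intervention status". The abstract also calls the target a main effect. The level is 5%, one-sided. A second step pools both arms in a one-way repeated measures ANOVA over time.
- **Factors of the primary test** (same section): three times crossed with randomised group, given as "with timing (pre-intervention, post-intervention, and 4 months post-intervention) and intervention status (intervention group and waiting group) as the independent variables".
- **Assessments** (Study procedure): "Outcome measures will be evaluated at three times (T1–T3) in the intervention group and four times (T1–T4) in the waiting group". On spacing, "the interval between T1 and T2, T2 and T3, T3 and T4 will be 4 months respectively".
- **What the waiting group's four times are** (abstract, Methods): "at the entry, before the intervention, at the end of the intervention, and 4 months after the end of the intervention". Its BA therefore falls between T2 and T3.
- **Hypothesis** (Power and sample calculation): "intervention group would have lower mean post-intervention scores on the BDI-II than waiting group". The same section says that "the minimal clinically important difference of the primary endpoint, BDI-II, is 3.5 points", with a standard deviation of 7.84.

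The analysis section does not say which three of the waiting group's four assessments supply the timing levels. It names neither the group-by-time interaction nor a contrast at T2.

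**The concern.** Randomisation gives a comparison of BA with no BA only while one arm is treated and the other is not. At T1 neither arm has had BA, and from T3 on both have. Only T2 carries the comparison that the hypothesis describes.

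A group main effect averages the arm difference over all three levels. It therefore mixes the one informative difference with others that are near zero by design, or it leaves that difference out altogether. An effective programme could give a null primary result because of the contrast chosen. The text also leaves open which of these two outcomes applies.

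**Working it through.** **Inputs from the protocol.** Difference δ = 3.5, SD σ = 7.84, r = 0.50, one-sided α = 0.05, 1:1 allocation, N = 38, dropout 10%. Analysed: 38 × 0.9 = 34.2, taken as 34, or 17 per arm. *Assumption:* r = 0.5 applies between every pair of visits.

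**The plan's own figure.** No formula is given for 38.
- A within-between interaction F test with f = (3.5/7.84)/2 = 0.223 gives 34 (two times at α = 0.10, or three times at α = 0.05). Then 34/0.9 = 37.8, so 38.
- A one-tailed paired t test gives 33. Then 33/0.9 = 36.7, so 37.
- A group main-effect F test with the same f and three times needs 86 (α = 0.10) to 108 (α = 0.05), or 96 to 120 with dropout.

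None of the main-effect calculations gives 38.

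**Expected benefit in each cell.** Let δ be the effect at the end of BA in either arm, and δf the effect remaining 4 months later.

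| Alignment | Arm | Level 1 | Level 2 | Level 3 |
|---|---|---|---|---|
| Calendar | Intervention (T1, T2, T3) | 0 | δ | δf |
| Calendar | Waiting (T1, T2, T3) | 0 | 0 | δ |
| Own intervention | Intervention (T1, T2, T3) | 0 | δ | δf |
| Own intervention | Waiting (T2, T3, T4) | 0 | δ | δf |

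**Calendar alignment.** Main effect = [0 + δ + (δf − δ)]/3 = δf/3.
- Full persistence (δf = δ): 3.5/3 = 1.17 points.
- Half persistence (δf = δ/2): 3.5/6 = 0.58 points.

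Power of the main effect under full persistence:
- SD of a three-visit mean = 7.84 × √((1 + 2 × 0.5)/3) = 6.40.
- SE = 6.40 × √(2/17) = 2.20.
- Noncentrality = 1.17/2.20 = 0.53, so power is 13% (14% with all 38 analysed). Half persistence gives 8% with 34.
- For 80% power, about 746 analysed patients would be needed.

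**T2 contrast adjusted for T1.**
- Residual SD = 7.84 × √(1 − 0.5²) = 6.79.
- SE = 6.79 × √(2/17) = 2.33.
- Noncentrality = 3.5/2.33 = 1.50, so power is 43% (47% with 38).
- For 80% power, 94 analysed patients are needed, or 105 with dropout.

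The gap remains for larger effects. In simulation with 17 per arm and full persistence, a true effect of 6 points gives 23% for the calendar main effect and 80% for the adjusted T2 contrast.

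**Own-intervention alignment.** The arm difference is 0 at every level, so main effect and interaction both have expectation 0. Simulation with 19 per arm gave a mean difference of 0.00 and rejection in 5.0% of runs. If both arms share a time trend with values g0 to g3 at T1 to T4, the main effect is (g0 − g3)/3, which is not a BA effect. With an assumed fall of 1 point per period this is (0 + 3)/3 = 1.0 point against BA, and simulated rejection was 1.6%.

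**Interaction.** Under calendar alignment the interaction carries the T2 difference. It is an F test on 2 degrees of freedom, with simulated power of about 27% at N = 38 under full persistence.

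**The case against.** The strongest reply is that main effect is loose wording for the treatment effect, and that the group-by-time interaction was meant. The Primary outcomes section asks about a difference between groups before and after the intervention, which is interaction language. The planned 38 can be reached from an interaction formula. This has weight, but no section names the interaction, and both the abstract and the analysis section say main effect. The interaction carries the T2 difference only under calendar alignment. As a non-directional test on 2 degrees of freedom, it does not match the one-sided 5% level.

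A reader might infer that the plan is bound to test a quantity equal to zero. The documents do not support that. The timing labels, read literally, follow each arm's own intervention. But the second step already pools patients on that clock, so the first step would largely duplicate it, which favours calendar alignment. The text settles neither.

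A reader might also infer that on own-intervention alignment no untreated waiting-group value is used. That is not so: the untreated T2 value enters, but as that arm's baseline rather than as the comparator for treated patients.

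The choice of model can be left to a statistical analysis plan. The effect, factors and levels are already fixed in the protocol, so a plan that follows them inherits the mismatch. The pooled one-way ANOVA does not repair it, because it is an uncontrolled pre-post comparison.

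**Conclusion.** The point stands. As worded, the primary test does not estimate the hypothesised post-intervention difference, and nothing elsewhere in the article corrects this. Its size depends on the alignment, which the article leaves open:

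- **Calendar:** one third of the effect remaining at T3. The 1.17 points and roughly 13% power assume full persistence to T3, an equal gain in the waiting arm, and r = 0.5 throughout. A fading effect makes the estimate smaller.
- **Own intervention:** expectation zero if there is no common time trend. With a trend, the estimate is trend alone.

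One third and zero are therefore values under stated assumptions, not fixed properties of the trial.

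**What to change.** Name one primary analysis: the between-group difference in BDI-II at T2, before the waiting group starts BA, adjusted for T1 BDI-II. Either ANCOVA or the T2 contrast of a mixed model would do, tested at the stated one-sided level. Say explicitly which waiting-group assessments enter each analysis. Report T3 and T4 as follow-up without a randomised untreated comparator. Preferably use the same T2 contrast for the secondary scales; these are labelled exploratory, so this is less pressing.

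T1 and T2 are scheduled in both arms, so no new assessments are needed. The cost is a documented amendment before the outcome data are examined. One should not assume that the data are already collected and only wording is at stake: the Trial status section reports 38 randomised by March 31, 2024 but plans to complete recruitment on March 31, 2025.

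The change raises power at 3.5 points from about 13% (calendar main effect) to about 43% with 34 analysed. That is still short of 80%, so the sample size justification must be revisited together with the primary analysis.

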#### Exclusion criteria

The exclusion criteria will be as follows: (1) severe physical or psychological symptoms (cognitive dysfunction [defined as a score of ≤ 23 on the MMSE-J performed for all prospective participants aged ≥ 65 years or those aged 20–64 years who did not seem to understand routine instructions during the preliminary interview], impaired consciousness, severe depression with psychotic symptoms, imminent suicidal ideation, and history of suicide attempt); (2) receipt of psychological intervention, such as BA, by mental health professionals before enrollment; (3) use or planned use of any psychotropic drug during the program, except for temporary emergency use after enrollment based on the discretion of the attending physician; (4) substance dependence based on the diagnostic criteria in the Diagnostic and Statistical Manual of Mental Disorders, 5th edition; and (5) difficulty in participating in this program due to other reasons, according to the attending physician or researchers.

The waiting group will be informed that if the need for medication arises during the waiting period, they will be excluded from the study but can be offered another program equivalent to the BA program if they wish.

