#### Discontinuation criteria

The discontinuation criteria will be as follows: (1) serious adverse events or adverse reactions that make it difficult to continue the intervention; (2) worsening of physical or psychiatric symptoms, or emergence of new symptoms that make it impossible to continue the intervention; (3) patient desire to discontinue the intervention; (4) interval of 1 month or more between sessions attended; (5) regular use of psychotropic drugs at the discretion of the attending physician during the implementation of the program or while waiting; (6) meeting the exclusion criteria while waiting; and (7) any other reason for which the attending physician deems it necessary to discontinue the intervention.

If this study will be discontinued, the date on which the decision for discontinuation was made and the reason for discontinuation will be noted on the case registration form. The data center will be informed of the discontinuation.

If serious adverse events or adverse reactions, such as worsening of psychiatric or physical symptoms, occurs and it is deemed difficult to continue the intervention, the therapist will promptly inform the research director at each research institution and discontinue this study. The research director at each research institution contacted will promptly inform the research representative and data center of the decision for discontinuation.

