### Study procedure

Information about the study will be communicated to each department of each research institution through postings, in-hospital e-mails, websites, and other means. The contact information of the research office will be clearly indicated. Patients who visit each research institution during the study period and wish to participate in the study after recommendation by their attending physician, and those who wish to participate in the study on their own and whose attending physicians determine that their participation is appropriate, will be selected from among those who meet the eligibility criteria and who do not meet the exclusion criteria. For patients who meet the eligibility criteria but not the exclusion criteria, the therapist will provide a detailed explanation during the preliminary interview and obtain their consent to participate in the study. Once consent is obtained, the therapist will confirm the eligibility and exclusion criteria other than the BDI-II score and ask the research assistant to administer questionnaires. The research assistant will ask the participant to fill out the BDI-II questionnaire and transfer the data (entry number, anonymized subject information, and T1 outcome data) to the data center with the entry number written on the case registration form. If the BDI-II score is 16 or higher, the patient will be registered in this study. Once a patient is registered, the registration will not be cancelled (deleted from the database) except in the case of withdrawal of consent, including refusal to use the data for research purposes. In the case of duplicate enrollment, the first enrollment information will be used.

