**Fig. 2 Fig2:**
[figure not shown]
SPIRIT figure: Schedule of enrollment, interventions, and assessments. *BDI-II* Beck Depression Inventory-II, *GAD-7* Generalized Anxiety Disorder-7, *FACT-G* Functional Assessment of Cancer Therapy-General, *FACIT-Sp-12* Functional Assessment of Chronic Illness Therapy - Spiritual Well-Being 12 Item Scale, *BADS-SF* Behavioral Activation for Depression Scale-Short Form, *VQ* Valuing Questionnaire, *NRS* Numerical rating scale, *IPOS* Integrated Palliative care Outcome Scale

Participants in the intervention group will be asked to complete questionnaires at three times (T1–T3). Participants in the waiting group will be asked to complete questionnaires at four times (T1–T4). They will complete questionnaires in the waiting room, at the examination room after the BA session at the facility, or at home. Research assistants will check the responses and ask participants to supply any missing data. The research assistants will collect the completed questionnaires. They will transfer the data from the questionnaires to the data center.

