#### Patient disadvantages and how to minimize them

Since this is a study examining the effects of BA, a behavior-focused psychotherapy, on depression in patients with advanced cancer, we believe that the physical and psychological disadvantages to the study participants will be minimal. However, we will give due consideration to their physical and psychological condition, bearing in mind that they might experience stress due to the content of the intervention program and questionnaires. If exclusion criteria are met during the waiting period, such as worsening of psychiatric symptoms, the patient’s participation will be stopped immediately, and appropriate medical treatment, such as a visit to the psychiatry department of each research facility, will be provided. In addition, patients with a BDI- II score of 21 (moderate) or higher will be enrolled if they wish to participate in the study after being fully informed that they might benefit from pharmacotherapy and the study will be terminated immediately and they will be switched to regular psychiatric care if they experience worsening of psychiatric symptoms based on the discontinuation criteria.

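### Stopping rules triggered by psychiatric worsening or need for medication are worded as ending study participation, and the article does not say that BDI-II collection continues afterwards

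*Protocol article*

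**What the plan says.** **Analysis.** Under Major statistical analysis, the protocol article takes "all randomly assigned subjects in the primary analysis set", applies the intention-to-treat principle to BDI-II, and adds: "When there is any missing data, we will employ multiple imputation".

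**Stopping rules.** Three statements govern patients who get worse:

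- Exclusion criteria, on waiting patients who come to need medication: "they will be excluded from the study but can be offered another program equivalent to the BA program if they wish".
- Patient disadvantages and how to minimize them, on waiting patients who meet an exclusion criterion, with psychiatric worsening as the example: "participation will be stopped immediately, and appropriate medical treatment" follows.
- The same section, on patients entering with BDI-II of 21 or higher, with no restriction to one arm: "the study will be terminated immediately and they will be switched to regular psychiatric care if they experience worsening of psychiatric symptoms".

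Discontinuation criteria lists related triggers. Worsening symptoms and regular psychotropic use apply in both arms; meeting an exclusion criterion while waiting applies to the waiting arm only.

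**What is kept.** On discontinuation, "the date on which the decision for discontinuation was made and the reason for discontinuation will be noted on the case registration form". Under Study procedure, "the registration will not be cancelled (deleted from the database) except in the case of withdrawal of consent". The article does not say whether BDI-II is still collected after stopping. It does allow questionnaires to be completed "at the examination room after the BA session at the facility, or at home".

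**The concern.** An intention-to-treat analysis needs outcome scores from patients who stop treatment or waiting as well as from those who complete it. The rules above do not separate stopping the programme or the wait from leaving the study. A site that follows them literally would plausibly stop sending questionnaires.

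The triggers, psychiatric worsening and need for psychotropic drugs, are related to the primary outcome. A patient removed for them probably has a higher later BDI-II than the baseline score predicts. Imputing that score from patients who stayed would make the affected arm look less depressed than it was.

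T2 matters most. It is the end of the programme in the intervention group and the end of the wait in the waiting group, so it is the last assessment at which the waiting group is still untreated. With 38 patients randomised 1:1, about 19 per arm carry that comparison, and one or two lost scores are a visible fraction. An analysis plan can choose how to impute, but it cannot recover scores that were never collected.

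**Working it through.** **1. The wording side by side.** The analysis section keeps all randomised patients, and Study procedure keeps their registration. Stopped patients therefore stay in the analysis set with the data already collected. The stopping rules speak of exclusion from the study, stopped participation and termination of the study. What the text secures at that moment is the registration, the date and the reason. Later BDI-II scores are neither promised nor forbidden.

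**2. Inputs for the size.** The plan gives no figure for this bias, so there is none to reproduce.

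- From the document: 38 patients, 1:1, so 38/2 = 19 per arm; SD 7.84; r = 0.50; target difference 3.5 points (Power and sample calculation; Fig. 1 for the ratio).
- Assumed: r is read as the T1–T2 correlation; 2 of 19 are lost in one arm and none in the other; missing T2 scores are imputed from T1 using the patients who remain in that arm.
- Varied: rho, the correlation between the tendency to be removed and the rise in BDI-II from T1 to T2.

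**3. Simple form.** If k of 19 patients are lost and their true T2 scores lie D points above the imputed ones, the arm mean is too low by (k/19) × D. For k = 2:

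- D = 5: 2/19 × 5 = 0.53 points
- D = 10: 2/19 × 10 = 1.05 points

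**4. Simulation.** In 40,000 simulated arms of 19, T1 and T2 are normal with SD 7.84 and correlation r. Patients are ranked by a score with correlation rho to their T1–T2 rise. The top k lose T2, which is replaced by the regression prediction from T1. Bias in the arm's T2 mean, in points:

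| r | k | rho 0 | 0.32 | 0.5 | 0.71 | 1.0 |
|---|---|---|---|---|---|---|
| 0.5 | 2 | 0.00 | −0.36 | −0.56 | −0.82 | −1.19 |
| 0.5 | 1 | 0.00 | −0.19 | −0.30 | −0.44 | −0.62 |
| 0.3 | 2 | 0.00 | −0.37 | −0.58 | −0.85 | −1.25 |
| 0.7 | 2 | 0.00 | −0.31 | −0.49 | −0.71 | −1.02 |

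As shares of 3.5 points (r = 0.5, k = 2): 0.36/3.5 = 10% and 0.56/3.5 = 16% for weak to moderate dependence; 0.82/3.5 = 23% and 1.19/3.5 = 34% for strong to perfect dependence.

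With 2 lost in one arm and 1 in the other (r = 0.5), the net shift is the difference of the first two rows: 0.17, 0.26, 0.38 and 0.57 points for rho = 0.32, 0.5, 0.71 and 1.0.

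**5. Against the trial's precision.**

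- Standard error of the T2 difference: 7.84 × √(2/19) = 2.54 points.
- With baseline adjustment at r = 0.5: 2.54 × √(1 − 0.5²) = 2.20 points.
- Weak to moderate dependence: from 0.36/2.54 = 0.14 to 0.56/2.20 = 0.25 standard errors.
- Perfect dependence: 1.19/2.54 = 0.47 to 1.19/2.20 = 0.54 standard errors.

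**6. Direction.** Waiting-arm losses make the control group look better and work against BA. BA-arm losses make the BA group look better and favour it. Equal losses roughly cancel.

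**The case against.** **Silence in a condensed article.** A full protocol, version 1.4, exists and is not shown. Whether assessments continue after discontinuation is conduct detail that an article may leave to it, and several discontinuation criteria speak only of continuing the intervention. This stands in part. A reader might infer that the protocol forbids further questionnaires, or that collection is known to stop; neither is stated. What remains is wording that the article does contain: exclusion from the study, and participation stopped at once.

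**No contradiction with intention to treat.** A reader might infer that removed patients fall out of the analysis. They do not: registration is kept unless consent is withdrawn, all randomised patients are analysed, and missing scores are imputed. This stands fully.

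**The imputation sentence is not at fault.** It names no missing-at-random assumption; the calculation above supplies one. The imputation model and any sensitivity analysis for informative missingness belong to the analysis plan, so their absence here is no finding. This stands.

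**The effect is small and its direction unknown.** Even the worst case is about half a standard error, and the 2-versus-0 split has no source in the document. The wording specific to the waiting arm would, if anything, work against BA. This limits the weight of the point but does not remove it, since the remedy is simple.

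**Collected scores are not clean either.** Removed waiting patients may be offered a programme equivalent to BA. If 2 of 19 took it before T2 and gained 3.5 points (an assumption), the waiting mean would fall by 2/19 × 3.5 = 0.37 points, similar to the low end of the bias being avoided. Such scores fit an intention-to-treat comparison, but this is a choice about what is estimated.

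**Conclusion.** The point holds as a matter of conduct wording. Rules triggered by worsening or by need for medication are phrased as ending study participation, and the article does not say that BDI-II continues. If sites act on that phrasing, scores would be missing for reasons related to depression and would have to be imputed.

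Under the assumed loss of 2 of 19 in one arm only, that arm's T2 mean would be too low by 0 to 1.2 points at r = 0.5, and by 0.4 to 0.6 points for weak to moderate dependence. The bias is zero if removal is unrelated to BDI-II change, for example when it follows physical decline unrelated to mood. All of this sits within a standard error of about 2.2 to 2.5 points.

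A reader might go further and infer that the trial is biased in favour of BA. The document does not support that: most triggers apply in both arms, the rules specific to waiting would work the other way, and no loss counts are given. The result is a worthwhile, cheap improvement rather than a defect that invalidates the analysis.

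**What to change.** 1. In Exclusion criteria, replace the first clause of the waiting-group rule, on exclusion from the study, with: *they will leave the waiting programme but remain in the study*. The offer of an equivalent programme can stay.
2. In Discontinuation criteria and in Patient disadvantages and how to minimize them, add: *After stopping for any reason, the scheduled BDI-II questionnaires continue at the planned time points, at home if needed, unless consent is withdrawn.*

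The safety actions (ending the wait or the programme, and referral to psychiatry) do not change.

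**Cost.** A few extra self-report questionnaires, which the article already lets patients complete at home; a protocol amendment, communicated to participants and ethics committee members as Research ethics approval and protocol amendments requires; and updated participant information, because the medication rule is something waiting patients are told. Scores after stopping will include rescue medication or the equivalent programme, which could shrink the T2 contrast, by about 0.4 points in the example above. Some patients will be too ill to answer, so some imputation will remain.
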